### Recruitment

Five PCHCs in Madrid will be recruited. A total of 187 PCHPs will be invited to participate in the study. Based on experiences in previous studies, we expect a participation rate of 45%, which means 84 participating professionals. If necessary, the number of participating PCHCs will be expanded to reach the required sample size. PCHPs will participate in the study on a voluntary basis after signing the informed consent form.

Each participating PCHP will recruit 8 patients with a quota for each disease (5 with CVD, 1 with PD, and 2 with AD) consecutively as they attend the office. After the recruitment of patients, their caregivers will be invited to participate. For independent patients, it will not be necessary to recruit a caregiver.

During the recruitment interview, the PCHP will provide all information about the study as a detailed verbal explanation accompanied by a patient information sheet, making sure that the patient understands it.

### Randomization

Once the participants have been selected, after the initial visit, the patients will be randomized by pathology. Patients included in the intervention group will be included together with their caregiver and PCHP, creating a participant unit (patient-caregiver-PCHP or patient-PCHP). There will be no masking in any phase of the study. Assignment will be performed centrally by the Research Support Unit of the Primary Care Management of Madrid.

Patients in the intervention group will be fitted with the TeNDER system device best suited to their needs and will be treated according to standard clinical practice. Patients in the control group will be treated according to standard clinical practice.

Subsequently, each PCHP will be informed of which patients have been assigned to each group; based on this, they will have a different role in each case (ie, using the TeNDER system with the intervention group and usual practice with the control group).

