## Methods

### Design

A multicenter, randomized, parallel-group clinical trial will be conducted with a follow-up of 2 months. The unit of randomization will be the patient.

This study protocol is part of a proposal with European funding under the European Union’s Horizon 2020 Research and Innovation Programme (grant 875325). The European consortium that developed the proposal is composed of different countries: Spain, Portugal, Italy, Slovenia, Greece, Germany, and Belgium [22].

The TeNDER project is developed in 4 European countries (Spain, Germany, Italy, and Slovenia). To account for the differences in the health systems of the participating countries and organizations, this research protocol refers to the primary care health centers (PCHCs) of the Madrid Health Service, which belongs to the Spanish public health system.

The TeNDER project brings together experts in technological development and users, including chronic patients, their caregivers, and primary care health professionals (PCHPs). Therefore, it will have an initial phase of cocreation in which the needs of the users will be explored. Based on the results, the technical team will work on improving and adapting the TeNDER system.

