### Sample Size

The European consortium that developed the proposal called for a sample size of 1766 patients (1031 in the control group and 735 in the intervention group) with the aim of using the TeNDER system to achieve an improvement in QoL, as measured by the Short Form–36 Health Survey (SF36) [23], of 6 points in the intervention group as compared to the control group.

According to previous studies, the SD for QoL score in the population with the chronic diseases under study (PD, AD, and CVD) ranges between 16 and 27 [23-25]. For the power calculation, we used the highest value of this SD. Therefore, the sample size will allow a power of 98.8% to detect ≥6 differences in the overall score of the SF36 questionnaire, if they exist. Calculations were performed with Epidat (version 4.2; Xunta de Galicia).

In the PCHC of the Madrid Health Service, as part of the European consortium, 534 patients will be included (380 in the intervention group and 254 in the control group). No differentiation by pathology will be established.

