### Data Analysis and Statistical Plan

A descriptive analysis of the characteristics of the participants will be performed with frequencies and percentages for qualitative variables and the mean (SD) or median (IQR) for the quantitative variables, according to their distribution. The mean difference in QoL score between the intervention and control groups will be studied with the corresponding 95% CIs at T1 (2 months). Differences in qualitative variables will be analyzed with the Pearson chi-squared test, and differences in normally distributed quantitative variables will be analyzed with the Student *t* test (2-tailed).

To study the effectiveness of the TeNDER System in improving QoL in patients, an explanatory linear regression model will be constructed. The dependent variable will be the mean difference in QoL score between the intervention and control groups at T1 (2 months). As patients will be recruited grouped by cluster (ie, PCHC), all the estimations will be performed with robust estimators. The analyses will be performed with Stata (version 14; StataCorp).

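### Patients are randomised by pathology, but the T1 comparison is described unadjusted and the regression is not said to include pathology; the cost is small and conservative, and the fix nearly free

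*Protocol article*

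**What the plan says.** The Design section fixes the level of allocation: "The unit of randomization will be the patient". The Randomization section adds that, after the initial visit, "the patients will be randomized by pathology", with central assignment. No blocks or other mechanics are described. The Recruitment section sets a quota per professional of five CVD, one PD and two AD patients. The Sample Size section closes, directly after the Madrid numbers, with "No differentiation by pathology will be established".

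The Data Analysis and Statistical Plan section gives the T1 mean difference in QoL between arms with a 95% CI, and says that "differences in normally distributed quantitative variables will be analyzed with the Student *t* test (2-tailed"). For effectiveness, "an explanatory linear regression model will be constructed". Its covariates are not listed. The one design feature this section takes into account is grouping by health center, through robust estimators. Pathology is not mentioned there, although the Direct Data Collection section records each patient's main disease.

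**The concern.** Stratified allocation keeps the disease mix nearly equal between arms, so differences between diseases drop out of the arm contrast. An analysis that ignores the strata still counts those differences as residual error. The reported standard error is then larger than the true one, the interval covers more often than its nominal 95%, and the test falls below its nominal level. A two-sample t test has no place for a stratum term. Robust errors by center are not designed to remove the disease component, because the disease strata cut across centers.

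At stake is precision in the primary comparison. There is also a matter of wording: a reader cannot tell from the article whether the factor used to allocate patients is meant to be used in estimating the effect.

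**Working it through.** **The plan's own figure.** Sample Size section: 1031 versus 735, difference 6, SD 27. With two-sided alpha 0.05 (my assumption; none is stated for the power calculation), SE = 27 × √(1/1031 + 1/735) = 1.303 and power = Φ(6/1.303 − 1.96) = 99.6%, against 98.8% stated. That is close enough to accept the inputs. It refers to the whole consortium, not to Madrid.

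**Inputs for Madrid.** 380 intervention and 254 control, as printed. They sum to 634, not the printed 534; I use the arm sizes. SD 27 is taken as the total SD across diseases. Stratum shares of 0.625/0.125/0.25 follow from the 5:1:2 quota. Disease means are **assumed**, because the article gives none.

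**Formulas** (large sample, constant allocation ratio within strata, no center clustering):

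- SE₀ = 27 × √(1/380 + 1/254) = 2.188, so 6/SE₀ = 2.742 and the unadjusted half-width is 1.96 × 2.188 = 4.29.
- f = between-disease variance / 27² (27² = 729).
- Coverage of the unadjusted interval = 2Φ(1.96/√(1−f)) − 1.
- Unadjusted power = Φ((2.742 − 1.96)/√(1−f)).
- Adjusted power = Φ(2.742/√(1−f) − 1.96).

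Worked case, means 60/45/50: overall mean = 0.625×60 + 0.125×45 + 0.25×50 = 55.625. Variance = 0.625×4.375² + 0.125×10.625² + 0.25×5.625² = 33.98. f = 33.98/729 = 4.7% and √(1−f) = 0.976. Unadjusted power = Φ(0.801) = 78.8%; adjusted power = Φ(0.848) = 80.2%.

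| Assumed CVD/PD/AD means | Between-disease variance | f | Unadjusted coverage | Power unadjusted | Power adjusted | Gain (points) |
|---|---|---|---|---|---|---|
| all equal | 0 | 0 | 95.0% | 78.3% | 78.3% | 0 |
| 60/50/55 | 12.5 | 1.7% | 95.2% | 78.5% | 79.0% | 0.5 |
| 60/45/50 | 34.0 | 4.7% | 95.5% | 78.8% | 80.2% | 1.3 |
| 65/45/50 | 67.2 | 9.2% | 96.0% | 79.4% | 82.1% | 2.7 |

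In the last two rows the unadjusted interval is about 2% and 5% too wide (1/0.976 and 1/0.953), and the type I error is about 4.5% and 4.0%.

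**At SD 16**, the lower end of the article's range, the same two rows give f of 13% and 26% and coverage of 96.5% and 97.8%. Power is then above 99% either way, so nothing of consequence is lost.

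**Simulation checks.**

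- Ordinary robust errors, 8000 replicates, PD and AD both 20 points below CVD: coverage 96.4% unadjusted and 95.1% adjusted.
- Same gap, allocation not stratified: 94.9% unadjusted. The miscalibration therefore needs stratified allocation.
- Center-cluster-robust errors, 3000 replicates, five equal centers, no center effect, t with 4 degrees of freedom, SD 27: unadjusted coverage 94.8% and 95.7% for the two main sets of means when allocation is stratified overall, and 95.0% and 95.3% when it is also balanced within center. In the balanced case, adjustment did not reduce the standard error (2.00 against 2.01).

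**The case against.** The strongest reply is that the regression lists no covariates at all, so pathology is neither included nor excluded, and a journal article may leave a covariate list to the full protocol or SAP. That stands. A reader might infer that pathology is left out of the analysis; the article does not say so. What is on the page is narrower: the mean difference and t test are described without adjustment, and the regression is not said to include the allocation factor.

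A reader might also take the Sample Size sentence on pathology as a rule for the analysis. Its position, right after the Madrid numbers, points to sample-size targets. It still sits awkwardly beside the quota and the allocation by pathology, and is worth rewording.

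Two further inferences fail. The 5:1:2 quota does not disturb the interval; only stratified allocation does. And the gain should not be measured from 78.3%, the power when pathology explains nothing, because stratified allocation raises the power of the unadjusted test as well.

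Finally, the planned errors are robust for health center. With five centers the coverage in simulation is close to 95%, and the precision gain can vanish. That stands too, and limits the size of the point.

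**Conclusion.** The point holds as a modest, inexpensive improvement and does not show that the analysis is invalid. It rests on three conditions: allocation by pathology means stratified allocation, pathology predicts SF36, and it is omitted from the T1 comparison. Under those conditions the error is conservative, so any reading that false positives are inflated is wrong.

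At SD 27 with 380 versus 254, nominal coverage is about 95.5% to 96.0% under the two main sets of assumed means, and nearer 95% with center-cluster-robust errors. The power forgone is about 1.3 to 2.7 points, about 0.5 point with means of 60/50/55, and none if pathology is not prognostic. The disease means are assumptions, so the mismatch between allocation and stated comparison is firmer than its size.

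**What to change.** 1. In the Randomization section, state that allocation is stratified by pathology, and name the strata. Patients may have more than one qualifying condition, and other dementias are eligible but absent from the quota, so say which stratum each such patient enters.
2. In the Data Analysis and Statistical Plan section, make the primary T1 comparison the linear regression with pathology (main disease as used at randomisation) as a fixed covariate, in place of the unadjusted t test.
3. In the Sample Size section, reword the sentence on pathology to say that the sample size is not set or powered separately by pathology.

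With three strata the cost is two degrees of freedom and a few sentences. Main disease is already collected.

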#### Direct Data Collection

Once participants have agreed to participate in the study, they will be scheduled for the baseline visit (T0). At this visit, baseline and tool cocreation data will be collected. The final visit (T1) will take place 2 months after the intervention. Data collection during both visits will take place at the PCHC or at the patient’s home and will be carried out as face-to-face hetero-administered interviews by 2 project nurses. Data will be collected through questionnaires, and interviews will be indexed in an electronic data collection record (eDCR).

The primary outcome variable will be the QoL of patients measured using the SF36 questionnaire [23]. This is a 36-item questionnaire that includes 8 domains: physical functioning, role limitations due to physical problems, bodily pain, general health perceptions, mental health, role limitations due to emotional problems, social functioning, and vitality. Eight domain scores and a summary score (range 0-100) can be obtained; higher scores indicate better health-related QoL (HRQoL). In addition, six Likert-type questions are used to collect proxy indicators of QoL related to the TeNDER system. These questions are related to the perception of improved autonomy, support, improved self-care, and safety. In addition, we will collect sociodemographic variables such as sex, age, and nationality from patients, caregivers, and PCHPs. Also, technology affinity among the 3 types of users will be collected through a single ad hoc question. Clinical information collected from patients will include their main disease and other chronic diseases. The degree of autonomy and the need for help will be studied through ad hoc questionnaires at T0 and T1.

For a description of the usability of and satisfaction with TeNDER system after the intervention, the validated System Usability Scale questionnaire [24,25] will be administered to patients, caregivers, and PCHPs.

Caregivers’ QoL related to the care provided and the perceived satisfaction with the care provided will be studied through an ad hoc questionnaire.

The questionnaires (at T0 and T1) are included in Multimedia Appendix 1.

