## Discussion

Previous studies on the use of technological tools by people with chronic disease have shown an improvement in their self-management, self-care, and adherence to therapy. However, few studies have examined all users involved in the care of chronic patients in their use of these tools.

The strength of this work is to investigate the use of a technological tool focused on health and self-care by, on one hand, patients with chronic disease older than 65 years, and on the other hand, their caregivers or family supporters, as well as, finally, the health professionals who are responsible for monitoring their health status, in particular the PCHPs. This clinical trial among patients with highly prevalent chronic diseases and the people most involved in their care will provide a more realistic view of how technology can be integrated into their lives as an aid to care.

Another strong point is the involvement of users in the development and improvement of the TeNDER system. To this end, this work includes a cocreation phase in which the needs of the users are explored in order to develop a system that is adapted to them.

The main objective of this study is to improve the QoL of chronically ill patients older than 60 years. Despite the difficulties of achieving this with a 2-month intervention, there are certain proxy indicators of QoL that are sensitive to improvement, and this can be reflected in the HRQoL. Therefore, ad hoc questions have been included as variables that aim to detect elements that have an impact on QoL, such as safety and autonomy.

Among the main limitations are that due to the nature of the intervention, the trial cannot be masked. This may result in participants who are in the intervention group perceiving an improvement in their health follow-up; therefore, the difference in score with respect to the control group will increase. Thus, we propose to look for an increase of at least 6 points in the main improvement variable (QoL). In the same sense, the use of the TeNDER system can also lead to an improvement in patients’ adherence to treatment, as they feel observed and monitored by the system (ie, the Hawthorne effect).

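### The reason given for having no masking does not cover the nurses who administer the SF36 at 2 months, so an avoidable interviewer share of bias is left on the primary outcome

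*Protocol article*

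**What the plan says.** Under Randomization the protocol article states: "There will be no masking in any phase of the study". The same section places allocation after the baseline visit ("Once the participants have been selected, after the initial visit, the patients will be randomized by pathology") and gives it to a separate body ("Assignment will be performed centrally by the Research Support Unit of the Primary Care Management of Madrid"). PCHPs are then told which of their patients are in which arm.

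Under Direct Data Collection, "The primary outcome variable will be the QoL of patients measured using the SF36 questionnaire". Collection at baseline (T0) and at 2 months (T1) "will be carried out as face-to-face hetero-administered interviews by 2 project nurses". On location: "Data collection during both visits will take place at the PCHC or at the patient’s home". The System Usability Scale is given after the intervention, and six Likert items linked to TeNDER are also collected.

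The Discussion gives the only reason for the absence of masking: "due to the nature of the intervention, the trial cannot be masked". It accepts that intervention patients may perceive better follow-up and that the difference from control will grow as a result. Its answer is to look for an increase of at least 6 points.

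**The concern.** Masking those who use the system and masking those who collect the outcome are separate questions. The protocol answers both with one sentence and argues only the first. SF36 answers are spoken to a nurse whom nothing in the plan keeps unaware of the arm. Tone, prompting and clarification can then differ between arms. This plausibly matters more where patients have cognitive impairment, and the trial admits Alzheimer patients with Mini Mental State scores of 19 to 28.

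Any such influence falls on the T1 measurement from which the treatment effect is estimated, most plausibly in favour of TeNDER. A larger sample does not reduce it.

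**Working it through.** **Step 1. Who needs to know the arm, on the protocol's own description?**

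| Role | Task stated | Does the task require knowing the arm? |
|---|---|---|
| Patient, caregiver | Use the devices and app (Intervention) | Yes |
| PCHP | Uses TeNDER with one arm, usual practice with the other (Randomization) | Yes |
| Research Support Unit | Assigns centrally (Randomization) | Yes |
| University engineering group | Technical support (Intervention) | Yes |
| Two project nurses | Questionnaires at T0 and T1 (Direct Data Collection) | No stated task requires it |

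The nature of the intervention accounts for every row except the last. Three tasks are not attributed to anyone: fitting the devices, helping with app installation, and telephone support.

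**Step 2. When can interviewer bias enter?** Randomization follows the baseline visit, so T0 answers cannot be affected by the assigned arm. Only the T1 interview needs protection.

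**Step 3. Does the 6-point threshold protect against it?**

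- *Where the 6 points come from.* Sample Size already gives 6 SF36 points as the consortium's target effect, with 1031 control and 735 intervention patients and SD 27. SE = 27 × √(1/1031 + 1/735) = 1.303. Two-sided 5% power = Φ(6/1.303 − 1.96) = Φ(2.64) = 99.6%, against the stated 98.8%. This is close, and nothing here rests on the gap. The 6 points are the design effect, with nothing added for bias.
- *How the result will be judged.* The Data Analysis section plans a between-group mean difference with a 95% CI and a regression model. It sets no 6-point criterion. The smallest difference whose 95% CI excludes zero is 1.96 × SE, treating patients as independent:

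| Madrid arms | SD | SE | 1.96 × SE |
|---|---|---|---|
| 380/254 | 27 | 2.188 | 4.3 points |
| 380/254 | 16 | 1.297 | 2.5 points |
| 380/154 | 27 | 2.579 | 5.1 points |
| 380/154 | 16 | 1.528 | 3.0 points |

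The stated arms, 380 + 254, sum to 634, while the stated total is 534. The last two rows assume the total is right and the intervention arm is 380, so control is 534 − 380 = 154. In every row a difference below 6 points can be significant. SD 16 and 27 are the ends of the range under Sample Size. The robust estimators planned for clustering by center could change these SEs.

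**Step 4. How much would masking the interviewer gain?** Write the expected T1 difference as δ + p + i, where δ is the true effect, p the patient-expectancy bias and i the interviewer bias. If the nurse still learns the arm in a fraction u of interviews, the difference becomes roughly δ + p + u·i. The gain is (1 − u)·i. The documents give no value for i or u, so no figure follows. Sample size does not appear in the expression.

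**The case against.** **Most of the bias may lie with the patient.** The SF36 is self-rated by someone who knows the arm, and the inflation that the Discussion concedes is participant expectancy. This stands. Masking the interviewer leaves that part untouched, and the Discussion's concession is not evidence of interviewer bias.

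**The limitation is disclosed.** It is, but only as a general impossibility of masking. Assessor masking is not discussed, and disclosure does not justify leaving the avoidable part in place. Nor is this a detail lost when a full protocol is condensed, because the article affirmatively excludes masking in every phase.

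**Masking would leak.** Smartwatches are worn, visits may be at home among sensors, and patients may mention the system. This stands as a limit on the gain.

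**Existing staff may not suffice.** Nobody is named for device fitting, installation help or telephone support. If the nurses share these tasks, roles must be split patient by patient. No extra staff is therefore an assumption.

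**Stronger readings that the documents do not support:**
- *A quantified false-positive rate.* With no true effect and an assumed bias b, the rejection probability is Φ(b/SE − 1.96) + Φ(−b/SE − 1.96). With arms 380/254 and b of 2 to 3 points this gives 15% to 28% at SD 27 and 34% to 64% at SD 16. The arithmetic is right, but b has no source in the document and mixes p with i, so these rates do not measure what masking would gain.
- *Extension to all 1766 consortium patients.* The article refers to the Madrid centers only and does not describe masking elsewhere.
- *That no questionnaire order is fixed.* The questionnaires are in an appendix that is not shown.
- *That the nurses are told the arm.* The text does not say so. It says only that nothing is masked.

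**Conclusion.** The point holds in a limited form. The stated reason for no masking does not extend to the T1 SF36 interviewers, and this leaves an avoidable interviewer share of bias on a subjective primary outcome. That share is of unknown size and is additional to participant expectancy. The 6-point threshold does not guard against it.

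That interviewer masking is feasible is an inference from four stated features: two nurses, central allocation after T0, allocation communicated to PCHPs, and technical support given by the engineering group. It assumes that for each patient at least one nurse can stay out of set-up and support. No stated sample size, power or error rate changes. This is a low-cost improvement worth making; it does not invalidate the design.

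**What to change.** Replace the masking sentence under Randomization with: *participants, caregivers and PCHPs unmasked; T1 SF36 interviewer not told the allocation.* Under Direct Data Collection add:

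- The T1 SF36 is taken by whichever project nurse had no part in that patient's set-up or support.
- It is completed before any TeNDER-specific, usability or satisfaction item. Where feasible the other nurse takes those items.
- After the SF36, the interviewer records a guess of the arm, so that the success of masking can be reported.

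In the Discussion, separate participant expectancy, which remains, from interviewer bias, and do not present the 6 points as a protection.

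Cost: scheduling between the two nurses, and some unmasking through worn devices, home visits or patient remarks. No new visits or instruments are needed; no extra staff is an assumption, to be checked against who fits the devices and supports the patients. Recruitment began in April 2021, so T1 interviews already done cannot be changed. For those, report whether the interviewer knew the arm.
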